	**Structural**		
		SRV^c^ or city	Geographic location of study participant
		Incarceration history	Recent history and frequency
		Structural discrimination	External homophobia [42], racism [47]
		Stigma	HIV-related, PrEP-related
**Other covariates**			
	Mobile phone and technology use		Pew research technology use questionnaire [48,49]
	Mobile app use over the study period		Log in attempts, HIV testing and PrEP use, proportion complete HIV testing plans, proportion requesting HIV or STI home-test kits
	HIV Negative Cascade		HIV or STI testing history, PrEP awareness, barriers to PrEP uptake, PrEP adherence [50], barriers to PrEP use

^a^PrEP: pre-exposure prophylaxis.

^b^STI: sexually transmitted infection.

^c^SRV: subject recruitment venues.

##### Primary Outcome Measures

To measure acceptability of the MyChoices app, we will use the SUS, a validated 10-item measure that assesses subjective usability of a system, or, in this case, an app [28]. It is scored from 0 to 100, and a score of ≥50 indicates that the app is acceptable [32]. To determine feasibility, we will use app analytics to determine whether at least 60% of individuals randomized to the intervention condition opened the My Choices app at least once after their initial introduction to the app by research staff. We will also assess the proportion of participants who complete their HIV testing plan (regardless of planned testing intervals)—a primary function of the app.

##### Secondary Outcome Measures

While this pilot study is not powered to examine the efficacy of behavioral outcomes, at each major assessment, participants will be asked to self-report on HIV testing in the previous 3-month interval. We will also assess self-report accuracy by obtaining medical release for HIV test results. Additionally, at each assessment, participants will self-report whether, in the past 3 months, they made and attended a clinic appointment for PrEP initiation, whether they were prescribed PrEP, and whether they utilized PrEP.

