**Figure 1 figure1:**
[figure not shown]
Theoretical model for the MyChoices app development. PrEP: pre-exposure prophylaxis.

For example, self-regulatory functions (eg, self-monitoring one’s HIV testing through development of testing plans) and self-efficacy (eg, belief that one can attain the goal to test regularly) are enhanced by facilitative environmental conditions [23,24] such as reminder systems. MyChoices uses multimedia capabilities and environmental influences to support self-regulation and self-efficacy by enhancing the feeling of control over one’s ability to get tested regularly for HIV and use PrEP. Brief surveys about sexual risk and protective health behaviors within the app are used to assist users in tracking and self-monitoring their behaviors and creating a personalized HIV testing plan. Quizzes, videos, and infographics as well as “Help me Choose” (a quiz to help recommend a preferred setting for HIV testing), “Ordering” (a Web-based store to order free condoms, condom-compatible lubricant, and at-home HIV test kits), and geofencing (using global positioning system [GPS] to notify users when they are near a test site and due for testing) functions are used to maximize self-efficacy around HIV prevention and uptake of PrEP.

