#### Intervention

##### Standard of Care Condition

Following completion of the baseline assessment via computer-assisted self-interviewing (CASI), participants in both conditions will receive written prevention material including recommendations for HIV testing and referrals to local HIV testing sites and prevention services.

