###### Self-Efficacy for HIV Testing and HIV Prevention

A number of components target self-efficacy by empowering YMSM to be confident that they can effectively manage engaging in HIV testing, PrEP uptake, and condom use. For example, quizzes, infographics, and GIFs that focus on the promotion of HIV prevention and regular HIV testing and that appeal to YMSM have been incorporated. Links to videos related to PrEP (eg, what is PrEP and talking to your doctor about PrEP), reasons for routine HIV testing, and the importance of engaging in care if one tests positive are included. The MyChoices app also allows users to order home-testing kits for HIV and STIs (syphilis and rectal and urethral gonorrhea and chlamydia) and different types of condoms and lubricants that can be shipped directly to them or to another more confidential location of their choosing via an arrangement with Amazon. Additionally, the app includes information on and links to testing sites and local PrEP clinics (eg, contact number, address, and testing hours) as determined using GPS technology, allowing men to locate clinics that are nearby their current location.

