###### Goal Setting and Environmental Influences

The MyChoices app allows users to create an individually tailored HIV testing plan by having them compare and choose different options (eg, antigen-antibody testing to identify very recent infection vs rapid testing at home or in a clinic for convenience and quick answers) and provides answers to questions about HIV transmission behaviors and testing history (Figure 4).

After an HIV testing plan is developed, users have the option to customize the timing and content of testing reminders (eg, users can select from a list of phrases or create their own reminder to ensure privacy). Geofencing technology provides users with notifications to test if in the vicinity of a testing location (based on their GPS location) during the testing timeframe.

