### Statistical Analyses

The primary analyses will summarize acceptability (mean score on the SUS) and feasibility (participants utilizing the app at least once during follow-up) of the app, overall for the intervention arm, with asymptotic normal 95% CIs. Point estimates for mean acceptability ≥50 and for proportion accessing the app >0.60 will be considered the minimum criteria for acceptability and feasibility, consistent with industry standards [28,32].

The primary efficacy analysis will compare HIV testing (defined by the proportion that self-reports at least 1 HIV test result during follow-up) between the study arms at 3- and 6-month follow-ups. Group differences in self-reported PrEP-related appointments and documented HIV test results will also be examined at each time point. Moreover, group differences in measures related to the SCT model constructs (eg, HIV testing self-efficacy) will be assessed. The distribution of all variables will be assessed, and appropriate tests will be conducted (ie, parametric chi-square test vs nonparametric Fisher’s exact test).

All analyses will use two-tailed tests of significance, with significance at alpha=.05. We will follow an intent-to-treat approach [52], analyzing participants in the study arm to which they were assigned. We will examine the equivalence of random assignment to groups with regards to key baseline characteristics, including sociodemographics, prior HIV testing patterns, and sexual risk-related variables. In the event that randomization does not work to balance these characteristics, we will assess whether baseline differences may account for differences in outcomes.

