## Discussion

Advances in mobile phone technologies have enabled YMSM to have immediate access to broad social and sexual networks. The proposed project responds to the increasingly widespread use of mobile technology in the United States. MyChoices is a theory-driven app that was developed by our interdisciplinary team of HIV clinicians, epidemiologists, behavioral scientists, and app developers based on feedback from a diverse sample of YMSM and will be refined and tested using scientifically rigorous research methods. Therefore, to our knowledge, MyChoices will be one of the first comprehensive, theory-driven HIV prevention apps designed specifically for YMSM. We anticipate that MyChoices will increase HIV testing and linkage to prevention services because it is developmentally appropriate and meets YMSM where they are, in an environment that is familiar and discrete.

Anticipated limitations of this protocol include the self-reported outcomes for HIV testing and PrEP uptake. We will explore obtaining more objective measures of HIV testing and PrEP uptake, including obtaining photographs of test results and PrEP prescriptions. Relatedly, by answering questions about their HIV testing history at follow-up assessments, self-reported outcomes may be influenced that could bias the results. However, the follow-up survey covers a number of topics, including mental health, stigma, and sexual behaviors, and the HIV testing questions are limited. As a result, we do not anticipate substantial misclassification. There is also a risk that participants in the intervention group may discuss with or even show the MyChoices app to participants in the standard of care group (eg, if friends or partners both enroll in the study). To reduce the risk of contamination, study staff will remind the participants at baseline not to discuss the app with peers who might be in the study.

If MyChoices demonstrates acceptability and feasibility in this pilot study, a multicity, 3-arm RCT of this app and another youth-optimized app (LYNX) versus standard of care will be conducted through iTech. If shown to be efficacious, the MyChoices app could be a scalable technology-based solution, with the ability to reach YMSM across the United States, while maintaining a “geographically individualized” feel with app content integrated with local prevention and testing activities.

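### Medical release is the only committed source of documented HIV tests and is not shown to capture home tests, which the app supplies to one arm only, so the documented comparison is likely to under-count app-arm tests

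*Protocol article*

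**What the plan says.** **Source of records.** Secondary Outcome Measures in the protocol article names one source beyond self-report: "We will also assess self-report accuracy by obtaining medical release for HIV test results".

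**Use of records.** Statistical Analyses then plans a comparison between arms: "Group differences in self-reported PrEP-related appointments and documented HIV test results will also be examined at each time point". The main efficacy comparison is separate and rests on self-report, "defined by the proportion that self-reports at least 1 HIV test result during follow-up".

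**What the app arm receives.** Theoretical Framework for Intervention describes "a Web-based store to order free condoms, condom-compatible lubricant, and at-home HIV test kits". The section on self-efficacy repeats the point: "The MyChoices app also allows users to order home-testing kits for HIV and STIs". Under Goal Setting and Environmental Influences, the options in the testing plan include "rapid testing at home or in a clinic for convenience and quick answers".

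**What the control arm receives.** Standard of Care Condition: "participants in both conditions will receive written prevention material including recommendations for HIV testing and referrals to local HIV testing sites and prevention services". No kits are mentioned.

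**Other sources.** The Discussion says: "We will explore obtaining more objective measures of HIV testing and PrEP uptake, including obtaining photographs of test results". This is an intention to look into the matter, not a commitment. App users can also log their own results, and app analytics count kit requests. Neither is named as documentation, and both exist only in the intervention arm.

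**The concern.** Home testing is one of the routes by which the app is meant to work. A medical release is suited to finding tests done in clinics, and the article does not say how a home result would reach a record. Controls are pointed towards testing sites, where a record is more likely. The chance that a true test is counted as documented may therefore depend on the arm, and the likely direction is against the app.

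Two readings are at stake. The documented comparison could show a smaller difference than the true one, or none, if the app shifts people to home testing. The accuracy check could also make true reports look false, mostly in the app arm, and so cast doubt on the self-report efficacy result. Study Design says that the pilot's information, preliminary efficacy included, bears on whether the app goes forward to a full trial. An outcome definition tried here may also be carried into that trial.

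**Working it through.** The article gives no testing rate by arm, no home-test share and no figure for documented tests, so there is nothing of the plan's own to reproduce. What follows is an illustration.

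**Inputs.** From the article: 40 participants in the app arm and 20 controls (Randomization), and an outcome of at least one test (Table 1, Statistical Analyses). Assumed: true proportions tested p_app and p_ctrl; h, the share of app-arm testers whose *only* test in the window was a home test that the release does not find; and h_ctrl, the same share in controls.

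**Formula.** Documented difference = p_app × (1 − h) − p_ctrl × (1 − h_ctrl).

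**Base case.** p_app = 50%, p_ctrl = 30%, h_ctrl = 0, true difference +20 points.

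| h | Documented, app | Documented, control | Difference (points) |
|---|---|---|---|
| 0% | 50% | 30% | +20 |
| 10% | 45% | 30% | +15 |
| 25% | 37.5% | 30% | +7.5 |
| 40% | 30% | 30% | 0 |
| 50% | 25% | 30% | −5 |

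In participants, 50% of 40 is 20 true testers in the app arm and 30% of 20 is 6 in controls. At h = 25%, 5 app-arm testers have no record, leaving 15/40 against 6/20.

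**Break-even.** With h_ctrl = 0 the documented difference is zero at h = 1 − p_ctrl/p_app. For 50% against 30% this is 1 − 0.30/0.50 = 40%. For 60% against 40% it is 33%, and for 70% against 50% it is 29%.

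**Sensitivity.**
- If 5% of control testers also test only at home, the base case at h = 25% gives 37.5 − 28.5 = +9.0 points instead of +7.5.
- If both arms truly test at 40% and h_ctrl = 0, then h = 25% gives 30 − 40 = −10 points where there is no difference.
- If every home tester also has a recorded clinic test, h = 0 and there is no distortion of the proportion tested at least once.

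**Accuracy check.** Suppose every report is true, p_app = 50% and h = 25%. Then 0.50 × 0.25 = 12.5% of the app arm (5 of 40) report a test that no record confirms. Among those reporting a test, 75% are confirmed. Overall agreement, counting true non-testers, is 37.5% + 50% = 87.5%. The article does not say which measure it would use.

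**The case against.** The strongest reply is that little rests on this comparison. The main efficacy analysis uses self-report, which can include home tests and needs no record. The primary outcomes are the usability score and app use. The pilot is declared unpowered for behavior, and the abstract and Discussion tie the next trial to acceptability and feasibility. This stands, and it limits the weight of the point.

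Second, the article never defines a documented test as a medical record alone, photographs are under consideration, and the full protocol may hold the definition. This stands in part. A condensed article may omit an operational definition. But this one names a single committed source and a comparison between arms, and the two do not fit the home testing that it describes.

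Third, the distortion is conditional. It needs participants whose only test was at home, and enough more of them in the app arm. The app also promotes clinic testing, through its clinic locator and location-based notices, and controls may obtain home tests elsewhere. This stands in full.

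A reader might therefore infer too much: that a release cannot find any home test, that the documented comparison is biased by a known amount or will show harm, or that the plan will score home-test reports as false and so invalidate the efficacy result. The documents support none of these. They give no home-only share and no scoring rule, and no rule lets the record check override self-report. In the base case the sign reverses only above a 40% home-only share.

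Filling the gap from app data would not help. Logged results and kit requests exist in one arm only, and a request does not prove a test.

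**Conclusion.** The point holds in a limited form. As the article stands, ascertainment of documented tests is likely to differ by arm. The app-arm count is likely to be too low to the extent that its participants test only at home, and the accuracy check may take true home-test reports for over-reporting.

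The size cannot be stated from the documents. The illustration depends on assumed testing rates, on no home-only testing in controls (except where varied), and on the release finding every clinic test and no home test. Under those assumptions a 25% home-only share removes 12.5 of 20 points. The self-report efficacy comparison and the acceptability and feasibility outcomes are not directly affected. This is worth correcting because the change is cheap, but it does not threaten the trial's main conclusions.

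**What to change.** 1. In the follow-up questionnaire, in both arms, record the date and setting (clinic or home) of each reported test. Table 1 already lists testing history and the items are not shown, so first check whether this is asked.
2. Label the record-based comparison as *clinic-documented tests* and show it beside self-reported home tests by arm.
3. Check self-report against medical records only for tests reported as clinic tests.
4. If the photographs mentioned in the Discussion are adopted, collect them identically in both arms and count them as documentation.

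The cost is one or two questionnaire items and, if adopted, a photograph upload. There are two drawbacks. Home-test reports without a photograph stay unverified, mostly in the app arm, so over-reporting there would escape the check; the report should say so. Requests for photographs may also add to the measurement reactivity that the Discussion already acknowledges.

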##### Tertiary Outcome Measures

All measures are outlined in detail in Table 1. In brief, congruent with our theoretical model, we will assess the following: (1) Self-regulation: perceived HIV and STI risk and transmission knowledge; (2) Self-efficacy: HIV testing, PrEP use, and condom use self-efficacy; and (3) Environmental influences: perceived utility of reminders for HIV testing. Each of these variables will mirror the content of the app, and we will adapt validated scales when available [51]. We will also assess individual (eg, sexual behavior and mental health), social (eg, social support), and structural (eg, incarceration and stigma) covariates. Finally, among those randomized to the MyChoices condition, we will use app analytic data to assess the frequency and duration of app use, content and functionalities most and least utilized, and requests for HIV or STI testing kits, condoms, and lube.

### Statistical Analyses

The primary analyses will summarize acceptability (mean score on the SUS) and feasibility (participants utilizing the app at least once during follow-up) of the app, overall for the intervention arm, with asymptotic normal 95% CIs. Point estimates for mean acceptability ≥50 and for proportion accessing the app >0.60 will be considered the minimum criteria for acceptability and feasibility, consistent with industry standards [28,32].

The primary efficacy analysis will compare HIV testing (defined by the proportion that self-reports at least 1 HIV test result during follow-up) between the study arms at 3- and 6-month follow-ups. Group differences in self-reported PrEP-related appointments and documented HIV test results will also be examined at each time point. Moreover, group differences in measures related to the SCT model constructs (eg, HIV testing self-efficacy) will be assessed. The distribution of all variables will be assessed, and appropriate tests will be conducted (ie, parametric chi-square test vs nonparametric Fisher’s exact test).

All analyses will use two-tailed tests of significance, with significance at alpha=.05. We will follow an intent-to-treat approach [52], analyzing participants in the study arm to which they were assigned. We will examine the equivalence of random assignment to groups with regards to key baseline characteristics, including sociodemographics, prior HIV testing patterns, and sexual risk-related variables. In the event that randomization does not work to balance these characteristics, we will assess whether baseline differences may account for differences in outcomes.

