### Phase 3: Pilot Randomized Controlled Trial

#### Study Design

A pilot RCT will be conducted at 2 iTech SRVs (Boston, MA, and Bronx, NY) to evaluate the feasibility and acceptability of the MyChoices app and examine the preliminary efficacy of the app in increasing HIV testing and PrEP uptake compared with a standard of care control group. This information will determine whether MyChoices moves forward to be tested in a full-scale efficacy trial planned with iTech. We will enroll 60 YMSM across 2 iTech SRVs who will be randomized to receive either the MyChoices app or standard of care. Participants will be followed for 6 months and will complete a Web-based assessment every 3 months (Figure 2).

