#### Randomization

Only participants who express interest in using MyChoices for HIV prevention, meet eligibility criteria, provide informed consent, and complete a baseline assessment will be eligible for randomization (see Figure 2). Randomization will be stratified by SRV [31] and will occur in a 2:1 ratio with 40 YMSM randomized to the experimental condition (20 at each SRV) and 20 randomized to the control condition (10 at each SRV). This allocation will allow us to efficiently gather additional data on app utilization. Randomization will be based on a pregenerated list created by the iTech Analytic Core statisticians, with random blocks of size 3 or 6, and will be accessed through a Web portal.

Men who are randomized to receive MyChoices will be given brief instructions on the purpose of the app, how to access it, and an overview of how to use it. Participants will be encouraged to explore all components of the app and use it routinely.

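### The normal-approximation 95% CI fixed for the app-use proportion (n=40) misstates precision if usage is about 90% or more; the feasibility criterion itself is unaffected

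*Protocol article*

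**What the plan says.** The Statistical Analyses section names the interval for both primary outcomes, the mean System Usability Scale (SUS) score and the app-use proportion. Each is reported "overall for the intervention arm, with asymptotic normal 95% CIs". Feasibility is binary: "feasibility (participants utilizing the app at least once during follow-up". The Primary Outcome Measures section counts only openings after the introduction by research staff.

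The denominator is the intervention arm. The Study Design section says "We will enroll 60 YMSM across 2 iTech SRVs", and the Randomization section says that allocation "will occur in a 2:1 ratio", giving "40 YMSM randomized to the experimental condition (20 at each SRV" and likewise at the other site.

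Success is judged on point estimates: a value "for proportion accessing the app >0.60 will be considered the minimum criteria for acceptability and feasibility". The interval plays no part in that rule.

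The protocol states no expected usage rate. It does restrict who is randomized: "Only participants who express interest in using MyChoices for HIV prevention" who also meet the other conditions. Under Participants, they must be willing to download the app. After randomization the intervention arm is encouraged to use it routinely.

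**The concern.** The Wald interval for a proportion is known to fail when the sample is small and the proportion is close to 0 or 1. Here the sample is 40. The people are selected for interest and willingness to download, and the event is a single opening in 6 months of follow-up, so a result near 1 is a realistic prospect.

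The interval is the only measure of uncertainty that the article attaches to the feasibility estimate. If usage is high, the sponsor may have to publish an interval that runs past 1 or has no width, or else depart from its stated method after seeing the data. Those planning the next trial would read the lower limit as better supported than it is.

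The method is stated in the text, so this is not a detail left to an unseen analysis plan. The allowance for Fisher's exact test in the same section concerns tests of group differences and supplies no alternative interval for a one-arm proportion.

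**Working it through.** **Inputs.** Total 60 and ratio 2:1 (Study Design, Randomization); two-sided 95% level (Statistical Analyses); criterion 0.60 (Statistical Analyses). The true usage proportion p is not stated. It is an assumption, examined from 0.60 to 0.99.

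**Reproducing the plan's figure.** 60 × 2/3 = 40, as stated.

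**Formulas.** With x users among n = 40, p̂ = x/n and z = 1.96:

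- Wald: p̂ ± z√(p̂(1−p̂)/n)
- Wilson: [p̂ + z²/(2n) ± z√(p̂(1−p̂)/n + z²/(4n²))] / (1 + z²/n)
- Clopper-Pearson: exact limits from beta quantiles

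Example, 38/40: √(0.95 × 0.05/40) = 0.03446, and 1.96 × 0.03446 = 0.0675. Wald is therefore 0.95 ± 0.0675, or 0.882 to 1.018.

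**Intervals by result**

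| Users | Wald | Wilson | Clopper-Pearson |
|---|---|---|---|
| 24/40 | 0.448–0.752 | 0.446–0.737 | 0.433–0.751 |
| 32/40 | 0.676–0.924 | 0.652–0.895 | 0.644–0.910 |
| 36/40 | 0.807–0.993 | 0.770–0.960 | 0.763–0.972 |
| 37/40 | 0.843–1.007 | 0.801–0.974 | 0.796–0.984 |
| 38/40 | 0.882–1.018 | 0.835–0.986 | 0.831–0.994 |
| 39/40 | 0.927–1.023 | 0.871–0.996 | 0.868–0.999 |
| 40/40 | 1.000–1.000 | 0.912–1.000 | 0.912–1.000 |

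**Exact coverage.** For each p, the Binomial(40, p) probabilities are summed over all x whose interval contains p.

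| p | Wald | Wilson | Clopper-Pearson |
|---|---|---|---|
| 0.60 | 94.6% | 96.6% | 96.6% |
| 0.70 | 93.0% | 94.4% | 96.1% |
| 0.80 | 90.5% | 92.8% | 97.3% |
| 0.90 | 91.4% | 94.3% | 97.0% |
| 0.925 | 80.4% | 97.2% | 99.1% |
| 0.95 | 86.8% | 95.2% | 98.6% |
| 0.975 | 63.6% | 92.2% | 98.3% |
| 0.99 | 33.1% | 93.9% | 99.3% |

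Coverage moves in steps because x is a whole number. On a grid of p, mean Wald coverage is about 93% for 0.60 to 0.80, 92% for 0.80 to 0.90, 89% for 0.90 to 0.95 and 67% for 0.95 to 0.99. The lowest Wilson value on that grid is 90.5%.

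**Where the loss comes from.** At p = 0.975 the Wald interval contains p only for x = 35 to 39. The zero-width interval at 40/40 misses it, and 40/40 has probability 0.975⁴⁰ = 36.3%. Hence 100% − 36.3% − 0.05% (x ≤ 34) = 63.6%. At p = 0.925 the 39/40 interval also misses, because its lower limit is 0.927.

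**How often an unusable interval arises.** The upper limit exceeds 1 at x = 37, 38 and 39, and the width is zero at x = 40.

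- p = 0.90: 40.8% + 1.5% = 42.3%
- p = 0.95: 73.3% + 12.9% = 86.2%

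**Widths, Wald against Wilson.** 24/40: 0.304 and 0.291. 34/40: 0.221 and 0.220. 35/40: 0.205 and 0.207. 38/40: 0.135 and 0.151. 40/40: 0 and 0.088. Wald is the wider of the two from 24/40 to 34/40 and the narrower from 35/40 upward.

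**The case against.** The strongest reply is that nothing hangs on this interval. The criterion is a point estimate above 0.60, the primary analysis is descriptive, and no test or progression rule uses the limits. Where Wald breaks down, the conclusion is not in doubt: at 37/40 the lower limit is 0.843 (Wald) or 0.801 (Wilson), both far above 0.60. Near the threshold Wald works adequately, with 94.6% coverage at 0.60 and 93.0% at 0.70. The first count whose lower limit clears 0.60 differs by one person: 30/40 for Wald (0.616) and 31/40 for Wilson (0.625). High usage is also an inference; the only benchmark in the document is 60%. Finally, a reader given the count and n = 40 can compute a better interval.

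All of this stands, and it sets the size of the point. It does not remove the point, because the stated method still gives impossible or zero-width limits for results that the design makes plausible.

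Three stronger readings are tempting but are not supported:

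- **That the interval could distort the decision to proceed.** The criterion ignores the interval.
- **That Wald always looks too precise.** From 24/40 to 34/40 it is slightly wider than Wilson.
- **That the SUS interval is faulty too.** With about 40 scores, replacing 1.96 by a t multiplier of about 2.02 changes the width by roughly 3%; no defect is shown.

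A score or logit interval also rests on asymptotic normality, but the text names neither, so Wald is the ordinary reading.

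**Conclusion.** The concern holds for the app-use proportion, conditional on high usage. Below about 0.90 the shortfall in coverage is modest (mean about 93% over 0.60 to 0.90). Above it the shortfall is large: 80.4% at 0.925, 63.6% at 0.975 and 33.1% at 0.99. Results of 37 to 39 of 40 give an upper limit above 1, and 40/40 gives no interval at all.

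The consequence is misreported precision of a primary outcome; the feasibility decision is unchanged. This rests on two assumptions: that asymptotic normal means Wald, and that usage of 0.90 or more is plausible given the entry conditions and the single-opening definition. The arithmetic is exact given n = 40. The point is minor to moderate: it should be fixed, but the trial does not depend on it.

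**What to change.** In the Statistical Analyses section, specify a Wilson (or Clopper-Pearson) 95% CI for the proportion using the app. Keep the normal-based CI for mean SUS, and leave the point-estimate criterion as it is.

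The cost is one line of text and one line of code, with no change to sample size or data collection. Wilson intervals will be slightly narrower than the planned ones from 24/40 to 34/40 and wider from 35/40 upward (by about 0.002 at 35/40, 0.016 at 38/40 and 0.088 at 40/40). Clopper-Pearson is wider than Wilson at every count from 24/40 to 40/40 and covers at 96% or more at all the values tabulated, so it is the conservative choice.

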#### Data Collection

Baseline assessments will be conducted at the enrolling clinical site using CASI, with all follow-up assessments at 3 and 6 months conducted off-site and through Web. At each major assessment, participants will complete a CASI-based assessment battery via a secure Web-based data entry system. Outcome domains and measures are described in Table 1.

**Table 1 table1:** Outcomes and measures for MyChoices pilot randomized controlled trial.

Domain			Description or scale

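### For the scale-scored theory constructs, the plan gives no stated role to the participant's own baseline score; prespecified adjustment would gain precision using data that appear to be collected already

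*Protocol article*

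**What the plan says.** Under Statistical Analyses, the protocol article plans that "group differences in measures related to the SCT model constructs (eg, HIV testing self-efficacy) will be assessed". It then says that distributions will be inspected and "appropriate tests will be conducted (ie, parametric chi-square test vs nonparametric" Fisher's exact). No model, covariate or effect measure is given for a scale score.

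The same section describes one use of baseline data. The arms will be compared on key baseline characteristics and, if randomization has not balanced them, the investigators will look at whether those differences could explain differences in outcome. The examples listed are social and demographic background, past testing and sexual risk. The SCT scales are not among the examples.

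On availability, Data Collection states that "Baseline assessments will be conducted at the enrolling clinical site using CASI" and that "At each major assessment, participants will complete a CASI-based assessment battery via a secure Web-based data entry system", with the measures set out in Table 1. That table lists three self-efficacy scales (testing, PrEP, condoms) and a perceived HIV or STI risk measure. The Randomization section makes a completed baseline assessment a condition of being randomized.

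**The concern.** A person's score on a self-efficacy or risk-perception scale usually depends partly on where that person started. If follow-up scores are compared between arms without the starting score, stable differences between participants stay in the error term and the arm difference is estimated less precisely than the data allow.

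The imbalance rule does not recover this. It adjusts only after a difference has been seen, so it gives up the gain whenever the arms look similar. It also makes the choice of model depend on the data, and the text does not point it at these scales.

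What is at stake is the randomized evidence on whether the app moves the attitudes it was designed to move. The construct measures based on app use (testing plan, reminders, geofencing) arise only in the app arm, so the scale scores carry most of the between-arm information on the theory. With 60 participants, free precision is worth having.

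**Working it through.** **Inputs from the protocol article**
- Sample size (Study Design): "We will enroll 60 YMSM across 2 iTech SRVs who will be randomized to receive either the MyChoices app or standard of care".
- Allocation (Randomization): "will occur in a 2:1 ratio with 40 YMSM randomized to the experimental condition (20 at each SRV) and 20 randomized to the control condition". Check: 60 × 2/3 = 40 and 60 × 1/3 = 20.
- Test level (Statistical Analyses): "All analyses will use two-tailed tests of significance, with significance at alpha=.05".
- Power: none is stated for these scales. Secondary Outcome Measures says "While this pilot study is not powered to examine the efficacy of behavioral outcomes". There is therefore no power figure to reproduce.

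**Assumptions (not in the documents)**
- Correlation r between baseline and follow-up score: 0.3 to 0.7.
- Scale SD = 1, so results are in SD units; no dropout.
- A difference of 0.5 SD, for illustration of power only.

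**Step 1: comparison without the baseline score**
- SE = √(1/40 + 1/20) = √0.075 = 0.274 SD.
- Difference detectable with 80% power = (1.960 + 0.842) × 0.274 = 0.77 SD.
- Power for 0.5 SD = Φ(0.5/0.274 − 1.96) = 45% (43% from the t distribution).

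**Step 2: comparison adjusted for the baseline score (ANCOVA)**
- The residual variance is multiplied by 1 − r², so SE = √(0.075 × (1 − r²)).
- Estimating one slope at N = 60 multiplies the variance by 1 + 1/(60 − 4) = 57/56 = 1.018. The net reduction is 1 − (1 − r²) × 57/56.
- Equivalent unadjusted sample size = 60/(1 − r²).

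| r | Variance reduction | Net of slope | SE (SD) | Detectable at 80% (SD) | Equivalent N | Power for 0.5 SD, normal (t) |
|---|---|---|---|---|---|---|
| none used | – | – | 0.274 | 0.77 | 60 | 45% (43%) |
| 0.3 | 9% | 7% | 0.261 | 0.73 | 66 | 48% (46%) |
| 0.5 | 25% | 24% | 0.237 | 0.66 | 80 | 56% (54%) |
| 0.7 | 49% | 48% | 0.196 | 0.55 | 118 | 73% (70%) |

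The SE, detectable difference, equivalent N and normal-based power leave out the small slope cost; the t-based power includes it. Simulating 20,000 trials of 40 versus 20 at each r gave variance reductions of 7.4%, 24.1% and 48.0%, in line with the net column. Site was not included in these calculations.

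**Step 3: change scores are not a substitute**
A change from baseline has variance 2(1 − r), which is 1.4, 1.0 and 0.6 at r = 0.3, 0.5 and 0.7. ANCOVA gives 0.91, 0.75 and 0.51. A change score does worse than the raw follow-up score at r = 0.3 and only equals it at 0.5.

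**The case against.** The strongest reply is that the article is silent here, and silence is not an error. It names no model for scale scores, a condensed article may leave the covariates of a tertiary outcome to an analysis plan, and nothing says that baseline scores will be left out. Chi-square and Fisher's exact tests cannot be the method for a self-efficacy score in any case. This stands as far as it goes: a reader might infer that a raw t-test has been fixed or that baseline scores are excluded, and the text supports neither. What remains is that the article does state a rule for baseline data, conditional on imbalance, and prespecified adjustment is better than that rule.

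Other stronger readings also fail:
- *The scale scores are shut out of the balance check.* The list of characteristics is introduced as examples, so it is open. The scores are not named, but they are not excluded.
- *Chance differences at baseline would pass for an app effect.* An unadjusted estimate does carry r times any baseline gap. Under randomization, however, that is ordinary sampling error, already allowed for in the 5% test level. The issue is efficiency.
- *These scales are the only test of the mechanism.* Table 1 also counts use of app components, the testing plan, reminders and geofencing-prompted testing among the SCT construct outcomes. They lack a between-arm comparison, but they are evidence on the theory.

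Baseline collection is also a reading of Data Collection together with Table 1, and is not confirmed scale by scale.

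**Conclusion.** The point holds as a free improvement in efficiency, limited to the three self-efficacy scales and perceived HIV/STI risk. It does not reach the app-use constructs, which have no baseline value.

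The size depends on a correlation that the documents do not supply. A reader might infer that a large share of the precision is lost whatever the scale; that is not supported. At r = 0.3 the gain is equivalent to about 6 extra participants (66 against 60), while at r = 0.7 it is close to doubling the trial (118 against 60). The figures also assume complete follow-up and that the scales are indeed scored at baseline.

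The consequences are limited. The article places these measures among its tertiary outcomes, and progression to the larger trial rests on acceptability and feasibility in the app arm. No go/no-go decision changes.

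**What to change.** State in the analysis text that each scale-scored construct will be analysed by ANCOVA at 3 and at 6 months: follow-up score on arm, with the baseline score of the same scale and recruitment site (the stratification factor) as covariates, regardless of any observed imbalance. Report the adjusted mean difference with its 95% CI. For these scales this replaces the imbalance-triggered check. One mixed model over both follow-up times is an optional alternative.

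Confirm that the four measures are in the baseline battery, and settle the wording before outcomes are examined by arm. If they are in the battery, the cost is a few sentences of analysis text: no new data, no added participant burden and no change to sample size.
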